### Recruitment

In a first screening (see Figure
1), roughly 17.000 families will be targeted through community records via two Dutch regional health care organizations (estimated response rate is 52%, see
[30]). All families will receive a personalized information letter, including the Eyberg Child Behavior Inventory (i.e., ECBI) to screen for children’s problem behavior
[30]. The criterion for inclusion will be a score at or above the 75^th^ percentile. This cut-off is chosen so that at-risk families will be selected, without excluding children and parents with subclinical or even normal-range functioning. Based on a conservative estimation, 889 families (10%) are expected to be eligible for inclusion. Additionally, a second screening will take place to check for exclusion criteria: mental retardation of the parent and/or child (IQ ≤ 70) and not mastering the Dutch language. Based on estimates from similar procedures followed in previous research
[31], 480 eligible families are expected to eventually participate in the ORCHIDS study. These families will receive a second invitation letter and will be contacted for trial participation.

**Figure 1 F1:**
[figure not shown]
Study design (CONSORT schedule).

### Randomization

Participants will be informed of the design of the study and will give consent prior to randomization. Randomization will occur through random selection of a participant number that is linked to either the intervention or control condition.

### Sample size calculation

Power analyses are essential to maximize chances to find significant G × E interactions
[32]. For this calculation, we used a Fixed Effects ANOVA Power Analysis in PASS11
[33]. Based on a meta-analysis that demonstrated a small effect size (*d)* of .20 of the IY intervention
[34], and assuming a small G x E interaction effect and no main effects of genes
[3,35,36], a sample size of *N* = 480 families will be required for investigating our hypotheses in a two-sided test at α = .05 and power (1-β) = .80.

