## Methods/Design

### Design

The ORCHIDS study is a randomized controlled trial with an intervention (i.e., the Incredible Years parent training) and a control condition that tests gene-based differential susceptibility to changes in parenting. Participants will be 480 families, with children aged 4–8 who show mild to (sub)clinical externalizing behavior problems. Of those families, 160 will be randomly assigned to the intervention condition and 320 families to the control condition. After enrollment in the trial and randomization, the baseline assessment (pretest) will be carried out. The Incredible Years (IY) program will be implemented after these baseline assessments. Participants in the control condition will receive no intervention, but are allowed –and, in case needed, are assisted– to seek mental health care and parenting support through regular services. Posttest and follow-up assessments will be conducted after 6 months and after 10 months, respectively. Approval for data collection was obtained from the central committee on research involving human subjects in The Netherlands (METC UMC Utrecht, protocol number 11-320/K).

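### The 80% power stated for 480 families does not follow from the method and effect sizes given; the stated calculation yields about 54–59% for a small effect

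*Protocol article*

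**What the plan says.** The Sample size calculation section of the protocol article names its tool: "we used a Fixed Effects ANOVA Power Analysis in PASS11". It takes d = .20 for the Incredible Years (IY) training from a meta-analysis and proceeds by "assuming a small G x E interaction effect and no main effects of genes". It concludes that 480 "families will be required for investigating our hypotheses in a two-sided test at α = .05 and power (1-β) = .80". The interaction is given no number. No carrier fraction and no correlation between measurements is stated.

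The Design section sets the allocation: "160 will be randomly assigned to the intervention condition and 320 families to the control condition". The Outcomes section makes moderation of the training effect by genotype the primary question. The Analyses section tests it as a group-by-genotype interaction, each factor with two levels, in a latent growth model. The Data collection section gives three waves: pretest, 6 months and 10 months.

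**The concern.** Method, training effect, alpha, sidedness, power and N are all printed, so the statement can be checked. A standardised difference of .20 normally needs close to 800 subjects in two equal groups for 80% power, and more at 1:2. An interaction of similar size is harder to detect than a main effect. A total of 480 therefore looked too small for the effects named.

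What is at stake is how a null result is read. From a trial described as 80% powered for a small interaction, a non-significant group-by-genotype term would count as fair evidence against differential susceptibility. If power for such an effect is materially lower, or was never calculated for the actual design, that reading is not justified.

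**Working it through.** **Inputs from the protocol article**
- N = 480, two-sided alpha .05, power .80, fixed-effects ANOVA, d = .20 for IY (Sample size calculation).
- 160 intervention, 320 control (Design).
- Two-level group by two-level genotype, so the interaction has 1 df (Analyses).

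**Assumptions, because the article gives no figure**
- A small interaction is f = .10, the equal-group equivalent of d = .20. In a balanced 2×2 layout the interaction has f = δ/4, where δ is the difference in training effect between carriers and non-carriers, so f = .10 means δ = 0.40 SD.
- Carrier fraction p is varied from 10% to 90%.

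**Formula.** Power = P(F′ > F crit), with F′ noncentral F on 1 and N − 4 df (N − 2 for two groups) and noncentrality λ = N·f². The critical value is 3.86.

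**1. Attempt to reproduce .80**
- f = .10, balanced cells: λ = 480 × .01 = 4.80, power **.59**. The first N to reach .80 is 787.
- .80 at N = 480 needs λ = 7.88, so f = √(7.88/480) = **.128**.

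**2. Training effect at the printed split.** This needs no assumption about the interaction.
- f² = (1/3)(2/3)(.20²) = .00889, so f = .0943.
- λ = 480 × .00889 = 4.27, power **.54**. At 1:2, .80 needs 885 families.

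**3. Interaction at 160:320**

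SE(δ) = √[1/(160p) + 1/(160(1−p)) + 1/(320p) + 1/(320(1−p))] in SD units, and λ = (δ/SE)².

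| Carriers | SE | Power, δ = 0.40 | Power, δ = 0.20 | δ for 80% power |
|---|---|---|---|---|
| 50% | .194 | .54 | .18 | 0.54 |
| 25% or 75% | .224 | .43 | .15 | 0.63 |
| 10% or 90% | .323 | .24 | .09 | 0.91 |

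At 50% carriers the detectable 0.54 SD is 0.54/0.20 = 2.7 times the overall training effect that the article assumes.

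**4. Joint test of group plus interaction (2 df)**
- Balanced, f = .10 for each: λ = 480 × .02 = 9.60, power .796.
- At 1:2, f = .0943 for each: λ = 8.53, power .744.

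**5. Illustration of the longitudinal design**

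Average the two post-baseline waves and adjust for baseline. Assume equal correlation r between all waves and the same effect at both later waves. The residual variance relative to a single unadjusted measurement is (1 + r)/2 − r². Take δ = 0.40, 160:320, 50% carriers, so λ = 4.27 divided by that factor.

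| r | Variance factor | Power |
|---|---|---|
| .3 | .56 | .79 |
| .4 | .54 | .80 |
| .5 | .50 | .83 |
| .6 | .44 | .87 |
| .7 | .36 | .93 |

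With 25% or 75% carriers, power is .71, .77 and .85 at r = .5, .6 and .7. With 10% or 90% it does not exceed .54.

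**The case against.** The strongest reply is that the interaction has no stated size, so the figure is unverifiable rather than wrong: an f of about .128 would give .80. That stands as a limit on the interaction figures, which are conditional on f = .10. It does not rescue the paragraph. The training effect and the split are both printed and give .54, and an undisclosed f of .128 would imply a 0.54 SD difference between genotypes in the actual design.

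A second reply is that the three listed assumptions, taken literally, describe a joint 2-df test, whose .796 rounds to .80. This may be how 480 arose. It needs balanced arms, which the trial does not have. It also rejects for a training effect alone, so it does not test the interaction.

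The third reply carries most weight. The planned analysis uses three waves, and repeated measurement with baseline information can raise power to .80 or above at 50% carriers. A reader might infer from .54 that the trial itself has coin-flip power. The documents do not support that: .54 describes an unadjusted single-occasion ANOVA, whereas the Analyses section plans a growth model. Equally, the gain in step 5 rests on correlations that the article does not give, shrinks with unequal genotype groups, and could differ for a test on slopes.

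A reader might also infer that dropout and the six candidate genes were wrongly ignored, since the number required equals the number in "480 eligible families are expected to eventually participate in the ORCHIDS study". An article may leave both allowances to the full protocol or analysis plan, so its silence is not an error. They belong in the recalculation as sensitivity inputs.

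**Conclusion.** The power statement is wrong as written. Under the stated fixed-effects ANOVA, 480 families give .54 for d = .20 at 160:320, without further assumption. For an interaction of f = .10 (assumed) they give .59 if balanced, and .54 down to .24 at 160:320 as the carrier fraction moves from 50% to 10% or 90%. If small means a 0.20 SD difference in training effect between genotypes, power is at most .18.

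This does not show that the planned longitudinal analysis lacks power, or that 480 is the wrong number of families. It shows that the 80% claim has no support in the calculation offered for it.

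**What to change.** Keep N = 480 and rewrite the paragraph to:
- state the interaction size as a difference in training effect between carriers and non-carriers, in SD units;
- recompute power for the group-by-genotype term at 160:320 over a range of carrier fractions, under the planned longitudinal model, with its assumed correlations and the contrast tested (slope or mean level);
- show sensitivity to loss to follow-up and to the alpha actually used across genes;
- report the difference detectable with 80% power. For the unadjusted single-occasion ANOVA this is 0.54 SD at 50% carriers; the figure for the planned model should come from the new calculation;
- drop the 80% claim for a small effect unless the new calculation supports it.

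The cost is a recalculation and one rewritten paragraph. It needs no extra families and no change of procedure. The downside is that the stated power may become less favourable, particularly for genes with few carriers or few non-carriers.

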### Intervention

The IY training is aimed at improving parenting skills in order to reduce child behavioral problems, such as aggressive behavior, and enhance competent behavior. The IY training includes 14 to 16 weekly two hour sessions. During these sessions parents watch video-vignettes, discuss parenting with each other and practice new techniques in role-plays. Each group will consist of approximately 10 to 12 parents. IY parent training is different from most other parent (management) training programs, in that trainers use a collaborative leading style: They do not instruct, but are part of the group and lead discussions
[3,37,38]. Many previous randomized trials have shown the program to be effective
[39], also in The Netherlands
[40]. Hence, IY parent training is an evidence-based parent training.

### Data collection

An overview of all measurement occasions is given in Table
1. Both the recruitment, as well as the waves of data collection will be conducted in two separate cohorts in 2012/2013 and 2013/2014. The recruitment (i.e., screening) will take place in September-October 2012 and 2013. The pretests will take place in November-January 2012 and 2013. Families will be asked to fill in questionnaires in the presence of a researcher or research assistant during home visits. Furthermore, parent–child interactions will be videotaped during structured play situations. This procedure will be repeated twice after the pretest, namely at posttest and follow-up. Saliva samples for genotyping will be collected once during pretest.

**Table 1 T1:** Overview of measurements

**Measurement**	**Screening**	**Pre test**	**Post test (6 months after baseline)**	**Follow up (10 months after baseline)**
Demographic characteristics		*		
Child behavior:				
External behavior (ECBI)	*	*	*	*
Prosocial behavior (MESSY)		*	*	*
Temperament: (CBQ)		*	*	*
Strengths and Difficulties (SDQ)		*	*	*
Genotyping *(DRD4, DRD2, DAT1, COMT, 5-HTTLPR, MAOA)*		*		
Parenting behavior:				
PPI		*	*	*
Parent-child interaction:				
DPICS-R		*	*	*

*Note*. *ECBI* Eyberg Child Behavior Inventory, *MESSY* The Matson Evaluation of Social Skills with Youngsters, *CBQ* Children’s Behavior Questionnaire, *SDQ* Strengths and Difficulties Questionnaire, *DRD4* dopamine receptor D4 gene, *DRD2* dopamine receptor D2, *DAT1* dopamine transporter gene, *COMT* catechol-o-methyltransferase gene = *5-HTTLPR* = serotonin-transporter gene, *MAOA* monoamine oxidase A gene, *PPI* Parenting Practices Interview, *DPICS-R* Dyadic Parent-Child Interactive Coding System-Revised.

### Outcomes

Primary outcomes are the possible moderating effects of child genotype on the IY intervention effect (i.e., on the decrease in externalizing problems behavior and/or increase in prosocial behavior of the child). The intervention effect will be assessed with the ECBI, the Matson Evaluation of Social Skills with Youngsters (MESSY
[41]), and the Dyadic Parent–child Interaction Coding System-Revised (DPICS-R
[42,43]), see measures in Table
1. Secondary outcomes will be the observed (changes in) emotional synchronization in parent–child interactions as possible underlying behavioral mechanism to the G × (G) × E interactions.

### Analyses

First, using independent *t*-tests, we will examine whether randomization was successful, comparing baseline levels of externalizing and prosocial behavior across the intervention and control condition. Possible significant differences at baseline will be used as covariates in analyses
[44]. Second, as the longitudinal data of individuals will be nested in families, multilevel latent growth curve analyses in Mplus
[45] will be performed. In this analysis, we will test the interaction between the variables ‘group’ (i.e., intervention vs. control) and ‘genotype’ (i.e., susceptible genotype vs. non-susceptible genotype) to examine possible G × E interactions. In addition, we will take into account families’ ethnic background (i.e., Caucasian vs. non-Caucasian) and additional parental support or (mental) health care families received during the study (i.e., additional self sought care vs. no additional self sought care). Ethnic background and additional care will both be used as covariates in the analyses.

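### Baseline covariates are chosen by significance tests between arms, so use of the pretest as a covariate is left to chance and precision is lost; fix the baseline adjustment in advance

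*Protocol article*

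**What the plan says.** In the Analyses section of the protocol article, independent t-tests come first: "we will examine whether randomization was successful, comparing baseline levels of externalizing and prosocial behavior across the intervention and control condition". The consequence is stated as a rule: "Possible significant differences at baseline will be used as covariates in analyses". Two other covariates enter whatever the data show: "Ethnic background and additional care will both be used as covariates in the analyses". No baseline score is on that unconditional list.

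The main model is described as "multilevel latent growth curve analyses in Mplus", and within it "we will test the interaction between the variables" for group and genotype. The section does not say whether the pretest is one of the growth-curve occasions.

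The Design section gives the allocation ("160 will be randomly assigned to the intervention condition and 320 families to the control condition") and places the pretest after randomization. The Sample size calculation section takes an effect "of .20 of the IY intervention". Table 1 shows the ECBI at screening as well as at the three later assessments.

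**The concern.** Whether a baseline variable belongs in the model depends on how strongly it predicts the outcome. The p-value for its difference between arms does not measure that. If randomization is sound and allocation has not influenced the pretest, any difference is chance, and the test rejects 5% of the time by construction. A non-significant result does not show that randomization succeeded. A significant one cannot separate bad luck from an effect of knowing the allocation, because the pretest comes after it.

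Three consequences follow:
- The final model depends on the trial's own data, and the pretest, usually a strong predictor of the same measure later on, is rarely chosen as a covariate.
- The tests compare whole arms, whereas the primary question is whether the intervention effect differs by genotype. Imbalance within genotype goes unseen.
- If the pretest is the first growth-curve occasion, a flagged pretest could serve both as outcome and as covariate in the same model.

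**Working it through.** **Inputs from the protocol article.** 160 v 320 families (Design); intervention effect d = 0.20, two-sided alpha 0.05, power 0.80, N = 480 (Sample size calculation); two baseline constructs tested (Analyses).

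**Assumptions.** The t-tests use two-sided 0.05. The baseline-outcome correlation r is not given, so 0.4 to 0.8 is shown. The share of children with a susceptible genotype is not given, so 30% to 50% is shown. Calculations use one pretest and one later measurement with equal SDs.

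**The plan's own figure.** N = 480 is not reproduced from d = 0.20 alone: a two-arm comparison with 80% power needs 786 in total at 1:1, or 884 at 1:2. The interaction effect is called small without a number, so this does not show an error, and nothing below depends on it.

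**1. How often a pretest is selected.** Per variable: 5%. For at least one of two, if independent: 1 − 0.95² = 0.0975.

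**2. What goes unflagged.** The SE of a standardized baseline difference is √(1/160 + 1/320) = 0.0968. The threshold is 1.965 × 0.0968 = 0.190 SD, or 95% of 0.20. A difference of exactly 0.20 gives p = 0.039 and is flagged. An unflagged imbalance between 0.10 and 0.19 SD occurs in about 25% of trials. If 15% of families lacked pretest data (136 v 272, assumed), the threshold would be 0.206.

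**3. Largest unflagged shift in the arm contrast**, given an imbalance just under 0.190 SD:
- pretest not used: r × 0.190 = 0.08 to 0.15 SD for r = 0.4 to 0.8
- change-type model: (1 − r) × 0.190 = 0.11 to 0.04 SD

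**4. Imbalance in the contrast of interest.** The baseline group by genotype imbalance has SE √[(1/160 + 1/320)(1/q + 1/(1 − q))], where q is the share with a susceptible genotype. That is 0.211 at q = 0.3 and 0.194 at q = 0.5. Chance alone gives 0.20 SD or more in about 34% and 30% of trials respectively. Within the susceptible subgroup, an arm imbalance of 0.20 SD or more occurs in 26% (q = 0.3) to 14% (q = 0.5). The planned t-tests look at neither.

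**5. Precision.** Relative variances are 1 for posttest only, 2(1 − r) for change, and 1 − r² with fixed baseline adjustment. Main-effect power at d = 0.20 is Φ(0.20 / (0.0968 × √variance) − 1.96).

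| r | Variance cut v change | Variance cut v posttest only | Power: posttest only | Power: change | Power: fixed adjustment |
|---|---|---|---|---|---|
| 0.4 | 30% | 16% | 0.54 | 0.47 | 0.62 |
| 0.6 | 20% | 36% | 0.54 | 0.64 | 0.73 |
| 0.8 | 10% | 64% | 0.54 | 0.90 | 0.93 |

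**6. Type I error.** The rule was simulated for the arm contrast (8,000 runs per setting; r = 0.5 and 0.7; posttest-only or change analysis unless the pretest was flagged, then baseline adjustment). It rejected in 3.5% to 4.9% of null trials. Fixed adjustment gave 4.9% to 5.1%.

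**The case against.** The strongest reply is that the plan is longitudinal. Outcomes are described as decreases and increases over three waves, so the pretest is probably a growth-curve occasion and contributes in every realisation. This largely stands. The fair comparison is then with a change-type model, and a reader who inferred a gain from 0.54 to 0.73 at r = 0.6 would be using a posttest-only analysis that the protocol nowhere plans. A growth model that already holds the arm means equal at pretest would gain less still. The Analyses section does not say which applies.

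Other stronger readings also fail:
- *Imbalances as large as the planned effect are ignored.* At full sample size 0.20 SD is just flagged; the blind zone ends at 0.19.
- *The rule inflates false positives.* The simulation shows it to be slightly conservative.
- *The power and bias figures apply to the primary test.* They concern the arm main effect. An arm imbalance shared by both genotypes largely cancels in the interaction. What carries over is the imbalance in step 4 and the lower residual variance.
- *The pretest is certainly used twice.* That holds only if it is an occasion and a flagged pretest enters the model for the same outcome.

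It can also be said that a pretest taken after randomization makes the comparison of some interest, since knowledge of allocation could affect scores or participation. That is fair, but it argues for describing the difference, not for letting a p-value choose the model.

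**Conclusion.** The point holds as a matter of efficiency and pre-specification. The protocol article states a covariate-selection rule that ignores prognostic strength, picks each pretest in about 5% of trials under valid randomization, misses arm imbalances up to 0.19 SD, and does not examine imbalance within genotype. For assumed r of 0.4 to 0.8, the residual variance forgone is about 30% to 10% if the growth model behaves like a change score, or 16% to 64% if the pretest is not an occasion. Lower residual variance would help the interaction test too. These sizes rest on the assumed correlation and on a single follow-up measurement. The documents do not support a claim of inflated type I error, and they do not establish that the trial is underpowered for its interaction, whose assumed size is not given as a number.

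**What to change.** Delete the t-test selection rule and state the following, whatever the observed imbalance:

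- Screening ECBI, the measure clearly taken before randomization, is a fixed covariate in all models.
- Each outcome's pretest is used in one pre-stated way: either as a covariate with posttest and follow-up as outcomes, or as the first growth-curve occasion, not both. If it is an occasion, say whether arm means are constrained equal at pretest.
- Baseline balance is reported descriptively by arm, and by arm within genotype, without p-values.
- A sensitivity analysis uses screening ECBI only as the baseline adjustment.

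The cost is a change of wording; every measurement is already planned, and the Trial status section says recruitment is still under way, so the change can precede analysis. There is a small downside. Because the pretest follows randomization, adjusting for it or constraining its arm means assumes that knowledge of allocation did not affect pretest scores or participation; the sensitivity analysis covers this. Screening ECBI is itself range-restricted by the 75th-percentile entry criterion, so it may predict less well than the pretest.

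### The stated nesting (families) leaves out the Incredible Years training groups, so intervention-versus-control standard errors are too small if outcomes correlate within those groups; the primary group × genotype test is largely unaffected

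*Protocol article*

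**What the plan says.** The Analyses section gives the reason for a multilevel model and names the level: "as the longitudinal data of individuals will be nested in families, multilevel latent growth curve analyses in Mplus". Within that model it names one test, the interaction of condition with genotype. The Outcomes section likewise makes moderation of the intervention effect by child genotype the primary outcome.

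Under Design, families are the unit of allocation: "160 will be randomly assigned to the intervention condition and 320 families to the control condition". Controls receive no programme from the trial.

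The Intervention section describes delivery in groups: "Each group will consist of approximately 10 to 12 parents". Over 14 to 16 weekly sessions the parents "discuss parenting with each other and practice new techniques in role-plays".

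The Sample size calculation section says "we used a Fixed Effects ANOVA Power Analysis in PASS11". It mentions no clustering.

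The first hypothesis (Aim and hypotheses) compares carriers in the intervention arm with non-carriers and also with control children. The second of these is an intervention-versus-control contrast.

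**The concern.** The family is the randomised unit. If each family contributes one index child (an assumption), a family level captures only that child's repeated measures and no dependence between families. The dependence that the design itself creates lies one level higher. IY families in the same training group share trainers, sessions and each other's influence for several months, while control families share nothing comparable.

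A model that stops at the family treats the 160 IY families as independent. If outcomes correlate within training groups, the standard error of any contrast between arms is understated, its confidence interval is too narrow and its test rejects too often. What is at stake is the overall intervention effect and the part of the first hypothesis that sets IY carriers against control children. The interaction test is at risk only under a further condition, examined below.

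**Working it through.** **Inputs.** From the article: 160 IY and 320 control families; groups of 10 to 12 parents in the IY arm only; d = 0.20; two-sided α = .05. Assumed, because the article does not give them: the training-group ICC (.01, .05, .10), the number of attending parents per family, and the carrier share (.3 to .5).

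**The plan's own figure.** N = 480 is given for a calculation "assuming a small G x E interaction effect and no main effects of genes", with a d "of .20 of the IY intervention", "in a two-sided test at α = .05 and power (1-β) = .80". It cannot be reproduced from d = 0.20. The standard error is √(1/160 + 1/320) = 0.0968, so the expected z is 0.20/0.0968 = 2.066 and power is Φ(2.066 − 1.960) = .54. As a one-degree-of-freedom interaction, 480 gives .80 at f = 0.128, but the article puts no number on the interaction. The figure is therefore neither confirmed nor refuted for the interaction, and this point does not rest on it.

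**Full-arm contrast.** With m families per training group, DE = 1 + (m − 1)·ICC applies to the IY arm only.
- Variance ratio, true to naive: (DE/160 + 1/320)/(1/160 + 1/320) = (2·DE + 1)/3.
- True type I error: 2·P(Z > 1.96/√ratio).

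If one parent per family attends, m = 10 to 12, which means 160/12 to 160/10, or about 13 to 16 groups:

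| ICC | DE | SE ratio | Type I error |
|---|---|---|---|
| .01 | 1.09–1.11 | 1.03–1.04 | .057–.059 |
| .05 | 1.45–1.55 | 1.14–1.17 | .086–.094 |
| .10 | 1.90–2.10 | 1.27–1.32 | .121–.137 |

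Worked line, m = 11 and ICC .05: DE = 1.5; ratio = 4/3; SE ratio 1.155; 1.96/1.155 = 1.697; type I error .090. A simulation (20,000 runs per setting, groups of 11, groups ignored in the analysis) gave .087–.091 at ICC .05 and .127–.129 at ICC .10, in agreement with the formula.

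If both parents attend, m = 5 to 6. The SE ratio is then 1.06–1.08 at ICC .05 (type I error .066–.070) and 1.13–1.15 at ICC .10 (.082–.090).

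Power of a valid test of d = 0.20 with m = 11 is Φ(2.066/√ratio − 1.960): .52, .43 and .36 at ICC .01, .05 and .10, against .54 without clustering.

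**IY carriers against control carriers.** A carrier shares a training group with about 10p other carriers (m = 11, carrier share p), so DE ≈ 1 + 10p·ICC, with the same variance ratio formula.
- ICC .05: DE 1.15 (p = .3) to 1.25 (p = .5); type I error .062–.070; simulated .061–.069.
- ICC .10: DE 1.3 to 1.5; type I error .074–.090; simulated .070–.088.

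Set against all 320 controls instead, the same arithmetic gives somewhat more: .065–.074 and .081–.098.

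**Group × genotype interaction (simulated, m = 11).**
- Group effect common to both genotypes: type I error .049–.051 at ICC .05 to .10. Genotype varies within training groups, so the shared effect largely cancels.
- Half the group variance genotype-specific, p = .3: .054 at ICC .05 and .067 at ICC .10.

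The simulation uses a single time point and is a simplification of the growth model.

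**The case against.** The strongest objection is that the plan's primary outcome and its only named model test are the group × genotype interaction, which is nearly immune. That stands. A reader might infer from the omitted level that the trial's main test is anti-conservative by the full-arm amounts. The documents do not support that: the interaction stays at about .05 unless training-group effects differ by genotype, and then moves only modestly. That condition is not far-fetched, because the trial's own hypothesis is that carriers respond more to their environment, but nothing in the article shows it.

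Second, the full-arm figures overstate the inflation for the carrier comparison in the first hypothesis, since each training group holds fewer carriers than families. This also stands, and the smaller figures are given separately.

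Third, the article counts parents, not families, and allows that one or more parents per family receive the training. Families per group may therefore be fewer than 10 to 12, with less inflation.

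Fourth, the ICC is unknown, and at .01 the effect is slight. This makes the size conditional; it does not justify omitting the level.

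Fifth, an article condenses a fuller plan, which might add the level. That is possible, and one-arm random effects are often left to such a plan. Here, however, the article states a nesting structure, and that statement would still need correcting.

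A reader might also carry DE = 1 + (m − 1)·ICC into the 480-family calculation. That would be wrong: the calculation concerns an interaction within which genotype varies inside training groups, so this design effect does not apply to it.

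**Conclusion.** The point holds in limited form. The article names the family as the nesting level and omits one-arm clustering by training group. For any positive training-group ICC, intervention-versus-control standard errors are then understated. Over ICC .01 to .10 with one attending parent per family, the naive standard error of the full-arm contrast is about 3% to 24% below the true one. The inflation is smaller if both parents attend and for the comparison of IY carriers with controls. The primary interaction test is largely unaffected unless training-group effects differ by genotype.

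The direction follows from the design. The size rests on an assumed ICC, on the number of parents attending per family and, for the carrier comparison, on an assumed carrier share. The change is worth making because it is cheap and protects contrasts that the first hypothesis uses. It does not call the primary test into question.

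**What to change.** - Record the training group of each IY family. The article reports the trial as still recruiting, so the identifier can still be captured.
- Replace the stated nesting with a partially nested growth model: a training-group random effect in the IY arm only, each control family as its own cluster, and small-sample degrees of freedom because there may be only about 13 to 16 groups.
- For the interaction, add a random genotype slope by training group as a sensitivity analysis.
- Apply 1 + (m − 1)·ICC only to power stated for an intervention-versus-control contrast, and give the assumed ICC and families per group alongside it. Do not apply it to the interaction power.

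The cost is one recorded identifier, a few lines of plan wording and somewhat wider intervals for the intervention contrasts.
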